### Intervention group: induction of labour at 41 + 0 or 41 + 1 weeks

Women randomised to induction of labour will be referred to the cooperating hospital for induction of labour according to local protocol. Induction of labour will be started at 41 + 0 to 41 + 1 weeks. Women with a cervix that is judged to be ‘ripe’ at vaginal examination (Bishop Score of 6 or more), will have labour induced with amniotomy followed by intravenous oxytocin according to local protocol. In case rupturing of membranes is not possible, cervical ripening will be accomplished in accordance with our national guidelines. In case the cervix is judged to be still unripe the day after priming, cervical ripening will be repeated. All patients in the intervention group will be monitored until after delivery.

### Control group: expectant management until 42 weeks

Women allocated to expectant management await spontaneous onset of labour until 42 weeks. If labour has not started, monitoring is according to local protocol. This reflects current care in The Netherlands. Monitoring can consist of consultations, electronic fetal heart rate monitoring and ultrasound assessment of amniotic fluid. An increase of the frequency of these checks as well as admission to the hospital is based on the judgment of the midwife or clinician in charge as usual. In the expectant management group, intervention will occur in case the fetal condition does not justify expectant management, such as reduced fetal movements reported by the mother, non-optimal fetal heart rate on CTG or oligohydramnios [12]. If an indication for induction of labour occurs, such as prelabour rupture of membranes for >24 hours or meconium stained amniotic fluid, referral to secondary care for labour induction is indicated according to the management strategies which are recorded in the national Obstetrical Indication List [41]. All diagnostic tests and interventions between randomisation and birth are registered in the case report form. Protocol violation is noted in the case report form with the reason of switch of policy to induction of labour. Women with uncomplicated pregnancies who are still in primary care will be referred to secondary care at 42 + 0 weeks for induction of labour following the procedure as stated for the intervention group.

### Outcome measures

#### Primary

Primary outcome will be a composite of perinatal mortality and neonatal morbidity. Adverse perinatal outcome is defined as a composite of perinatal mortality, a 5-minute Apgar-score below 7 and/or an arterial pH below 7.05 (as in other Consortium studies [32, 33]), meconium aspiration syndrome, plexus brachialis injury (with and without association with shoulder dystocia (additional manoeuvres to deliver shoulders)) and/or NICU admission (level of care and duration). Meconium aspiration syndrome is defined as respiratory distress in the first four hours after birth in presence of meconium stained amniotic fluid and categorised as severe (requiring assisted mechanical ventilation) or moderate (requiring oxygen for at least 48 hours or at a concentration of 40 percent or greater but without mechanical ventilation).

#### Secondary

Secondary outcomes will be maternal outcomes such as operative delivery (operative vaginal delivery, Caesarean section), need for analgesia (epidural, remifentanil, pethidin), post-partum haemorrhage ≥ 1000 ml and severe perineal injury (third- or fourth-degree perineal tear).

Maternal preferences, satisfaction, wellbeing and anxiety will be assessed alongside the trial [42, 43].

### Measurements

When a patient fulfils the study criteria and written informed consent is obtained, clinical data such as age, height, weight before pregnancy, ethnicity, highest finished education and social economic status based on postal code are collected at study-entry [44]. Obstetric history and level of care in current pregnancy are registered. Cervical ripeness will be assessed by digital examination of the cervix. The acquired Bishop score (based on dilatation, effacement, consistency, position and engagement) will be noted and fetal condition will be checked according to local protocol. Eligible women will be randomised subsequently.

After randomisation, number and lengths of admissions is noted. In the expectant management group, level of care and number of (outpatient clinic) visits is reported. At each visit, maternal and fetal assessments are recorded.

At the onset of labour all relevant data will be collected including start of labour. Data on first, second and third stage of labour are collected, including treatment for pain relief, mode of delivery and adverse perinatal and maternal outcomes.

Perinatal and maternal mortality and morbidity will be specified.

Data will be collected until women and child are discharged home for the first time or when deceased. If a participant withdraws from the study, the reason (lost to follow up, withdrawal of consent, prematurely stop of study) will be registered.

We will use standardised case report forms that have been established in previous studies.

Apart from the collection of clinical data, a sub-cohort of women will complete questionnaires addressing health related quality of life and wellbeing (EQ 6D [45], state anxiety (STAI [46]), preferences and satisfaction (SSQ [47, 48], LADY-X [49]), as well as questionnaires containing information on pain (PCS [50], NPRS/VAS) [51, 52]. Questionnaires will be completed at baseline after randomisation, and 6 weeks after delivery. Women can fill out the questionnaires online or on paper.

Women who do not give consent for randomisation will be treated according to the local protocol and they will be followed in a prospective cohort study.

### Follow up of women and infants

The last questionnaires will be filled out at 6 weeks post-partum. Informed consent will be asked for future follow up studies.

### Procedures, recruitment, randomisation and collection of baseline data

Randomisation will be performed through ALEA, a web-based software program for randomisation in clinical trials. The database is located in the central data collection unit in the Academic Medical Center in Amsterdam. Randomisation procedure is by individual randomisation. Women will be randomly allocated to either induction of labour or expectant management. We will collect data from women who refuse randomisation due to a strong preference for one of the treatment options or because they want to follow local policy. The study will be an open label study, as it is impossible to blind the health care workers and patients for the strategy to which the woman is allocated.

### Data safety

This nationwide trial will be carried out by midwives (primary care) and gynaecologists (secondary care). To ensure the quality of this study and to minimize the protocol violations, a website is launched with all study information. All sites will be informed by the researchers on the procedures. All sites have the possibility to consult (in person or by phone) the researchers of the study group and an email address is available for non urgent questions. All data are entered by research midwives or research nurses or trained medical students. After 900 inclusions, an interim analysis will be performed on safety. The operating procedures of the study are discussed with a data safety monitoring board, an independent group of experts who gave their approval to the design of the study safety.

### Serious adverse events

The following serious adverse events (SAE) will be identified: Perinatal death, maternal death, severe neonatal morbidity (NICU admission), severe maternal morbidity (IC/CCU admission), event related to induction of labour and uterine rupture, asphyxia and meconium aspiration with admission of the neonate on the NICU/High Care department. The Data Safety Monitoring Board will be informed if three SAE of the neonate will occur or one maternal SAE. All SAE are reported to the main investigators within 24 hours. They will report to the data safety monitoring board.

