The 41-42 weeks dilemma considers a large proportion of pregnant women, as with a policy of labour induction at 41 weeks 18% (31,166/173,099) of all pregnant women in The Netherlands would be induced, compared to 1.5% (2,525/173,099) at 42 weeks [37]. With a policy of expectant management 68.7% will have spontaneous onset of labour between 41 + 0 – 41 + 6 weeks [37]. Before the introduction of the most recent guideline on management of post-term pregnancy in 2007 [38], there were less inductions of labour between 41 + 0 and 41 + 6 weeks (2006 18,2% (30,903), 2007 18,0% (30,151) and more deliveries after 42 weeks (2006 4,9% (8,312), 2007 4,5% (7,550)) [39].

Because of the controversy on this issue between caregivers, and the fact that the policy in surrounding countries is different, we feel that a nationwide randomised clinical trial is the obvious and necessary step to come to a multidisciplinary guideline regarding (impending) post-term pregnancy. We will conduct a randomised controlled trial to evaluate the effectiveness of a policy of labour induction at 41 weeks compared to expectant management until 42 weeks in women without contra-indications for expectant management.

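### One serious-adverse-event category is defined by attribution to induction, so a serious event outside the other listed criteria can be an SAE in an induced labour but not in a spontaneous one

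*Protocol article*

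**What the plan says.** The section Serious adverse events of the protocol article lists perinatal and maternal death, neonatal intensive care admission, maternal IC/CCU admission, and asphyxia and meconium aspiration with neonatal admission. Between these stands "severe maternal morbidity (IC/CCU admission), event related to induction of labour and uterine rupture". The article does not say which events qualify as induction-related, and it gives no matching item for spontaneous labour. The wording also leaves open whether uterine rupture stands alone or is tied to induction.

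Four other places bear on the point:

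- **Use of SAEs.** The same section sends SAEs to the data safety monitoring board, with notification after three neonatal SAEs or one maternal SAE, not split by arm. Data safety adds: "After 900 inclusions, an interim analysis will be performed on safety". It does not name the measure.
- **Blinding.** Procedures, recruitment, randomisation and collection of baseline data states: "The study will be an open label study, as it is impossible to blind the health care workers and patients".
- **Onset of labour.** Background states: "With a policy of expectant management 68.7% will have spontaneous onset of labour between 41 + 0 – 41 + 6 weeks".
- **Induction in the control arm.** The control-group section provides for induction on indication before 42 weeks, and at 42 weeks by the intervention-group procedure. The category can therefore apply in both arms, but to different shares of them.

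**The concern.** An SAE definition used to compare two policies should capture the same event in the same way under both. Here one item depends on whether labour was induced, which is what the randomisation sets out to change. A serious peripartum event that meets no other listed criterion becomes an SAE if labour was induced and unblinded staff judge it related. The same event after spontaneous onset does not.

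If the board at 900 inclusions, or the final report, sets SAE numbers side by side by arm, part of any excess under induction in this category would come from the definition. A reader could not separate harm caused by induction from events that were merely labelled because induction took place. Reporting the category on its own line later would not recover the spontaneous-labour events that were never reported as SAEs.

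**Working it through.** **Figures from the article.** The percentages in Background reproduce: 31,166/173,099 = 18.0% and 2,525/173,099 = 1.46%, stated as 1.5%. The arm size also reproduces: 2 × 0.03 × 0.97 × (1.645 + 0.842)² / 0.02² ≈ 900 per group. The point does not depend on the sample size; it only scales the illustration below.

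**Expectant arm.** The share without spontaneous onset in the 42nd week of pregnancy is 1 − 0.687 = 31.3%. This is a ceiling for induction, since the remainder may include planned Caesarean section or spontaneous onset at 42 weeks. A lower share would raise the ratios below.

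**Induction arm.** The article gives no share actually induced. Women are approached at 40+5 to 41+0 and induced at 41+0 or 41+1, a gap of 0 to 3 days in which some will go into labour. I assume a constant daily rate h of spontaneous onset and take two values from the Background figures:

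- Lower: h = −ln(0.313)/7 = 0.166.
- Upper: 2,525/31,166 = 8.1% remain at 42 weeks, so the total rate is −ln(0.081)/7 = 0.359. The spontaneous part is 0.359 × 0.687/(1 − 0.081) = 0.268.

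The share still to be induced after t days is exp(−h·t). The exposure ratio is that share divided by 0.313.

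| Gap (days) | Induction arm induced | Ratio to 31.3% |
|---|---|---|
| 0 | 100% | 3.2 |
| 1 | 76–85% | 2.4–2.7 |
| 2 | 58–72% | 1.9–2.3 |
| 3 | 45–61% | 1.4–1.9 |

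The range is therefore about 1.4 to 3.2, and the direction does not reverse. The low end is cautious, because it removes early labours from the induction arm but leaves the expectant arm at 31.3%. With a three-day gap, two of those days fall before 41+0 in both arms. At the upper h the expectant share would then be 0.585 × 31.3% = 18.3%, and the ratio 44.7/18.3 = 2.4.

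**Illustration only.** Assume the same 1% risk of a residual event in every labour, every such event in an induced labour judged related, and 900 women per arm. The expectant arm records 900 × 0.01 × 0.313 = 2.8 events. The induction arm records 900 × 0.01 × 0.95 = 8.6 at 95% induced, 6.3 at 70% and 4.1 at 45%. Counting alike in both arms would give 9 against 9. The 1% risk and full attribution are not in the article. Less complete attribution reduces the gap.

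**The case against.** The strongest reply has four parts.

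- **No by-arm SAE comparison is stated.** This is correct. The article describes an interim safety analysis without a measure and a trigger that is not split by arm. A board charter or the full protocol may settle the tabulation. The conclusion must therefore be conditional. The definition itself is stated text, however, and later tabulation cannot restore events that were never reportable.
- **The main harms are already counted alike.** This is also correct. Death and NICU or IC/CCU admission do not depend on onset of labour. Nor do the primary composite, operative delivery, haemorrhage of 1000 ml or more and severe perineal injury. Labour data are collected for all women, and the trial analysis is by intention to treat. The problem is confined to residual events. Collecting data on all women still does not make a residual event in spontaneous labour reportable to the board as an SAE.
- **More induction-caused harm under induction is a real effect of the policy.** I agree; that excess is not bias. The bias lies only in not counting the same event when labour starts spontaneously.
- **The size rests on assumptions.** A reader might infer that nearly every induction-arm labour enters the category. The article does not say so, and its consent window and onset figures point lower. An event must also be judged related before it counts.

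A reader might go further and infer a high chance of a falsely significant safety signal. Under Fisher's test at 900 per arm that chance is 42–67% with an assumed 2% risk and 80–100% induced. It is 6–18% with 45–60% induced, and 5–11% with 0.5% risk and 80–100% induced. The article plans no such test and gives no such risk, so these figures are not a finding.

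**Conclusion.** The point holds in a limited form. One SAE category depends on attribution to the randomised procedure, is judged open label and has no counterpart in spontaneous labour. For serious events that meet no other listed criterion, the opportunity to be counted is about 1.4 to 3.2 times as great in the induction arm. This rests on 68.7% spontaneous onset under expectant management, a constant daily onset rate and a gap of 0 to 3 days before induction. Any by-arm reading of SAEs that includes this category would lean against induction.

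The documents do not support saying that the trial's safety comparison as a whole is tilted, because no by-arm SAE comparison is described and the gravest events are counted neutrally. The primary and secondary results are untouched. The change is worth making because it is cheap and because the loss of events cannot be repaired at analysis.

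**What to change.** - Replace the induction-related category with serious intrapartum and peripartum events defined by what happened. Report them as SAEs in every woman from randomisation, whatever the onset of labour or allocated arm.
- State whether uterine rupture is an SAE in its own right.
- Record relatedness to induction as a separate descriptive field, not as a condition for reporting.
- Base any by-arm safety comparison, at 900 inclusions or in the final report, on these arm-neutral counts by allocated arm. Do not filter on relatedness.

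The cost is rewording one SAE category and one case report form item, and a few more SAE reports from spontaneous labours, mostly in the expectant arm. No extra women, visits or procedures are needed.

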### Ethical consideration and trial registration

This study has been approved by the national central committee on research involving Human Subjects (CCMO- NL 38455.018.11), by the Medical Ethical Committee, Academic Medical Center, Amsterdam the Netherlands (METC: 2011/361). The study will be a multicenter randomised controlled trial. The participating hospitals got approval of their local boards. The trial was registered at the Dutch Trial Register (Nederlands Trial Register): NTR3431.

### Statistical issues

#### Sample size calculation

Sample size was calculated for non-inferiority testing using software Queary Advisor 7.0. Based on the incidence of the composite adverse perinatal outcome, the sample size is calculated at 900 women per group (1800 women in total) [53]. With this sample size, a two-group large-sample normal approximation test of proportions with a one-sided 0.050 significance level will have 80% power to reject the null hypothesis that labour induction and expectant monitoring are not equivalent (the difference in proportions, is 0.020 or further from zero in the same direction) in favour of the alternative hypothesis that the proportions in the two groups are equivalent, assuming that the expected difference in proportions on composite adverse perinatal outcome is 0.000 and the proportion in the standard group is 0.030.

When there is no equivalence this sample size (900 patients per group) will allow us to have 85% statistical power to detect 2% reduction in the risk of composite perinatal mortality and neonatal morbidity from 3% to 1%.

#### Data analysis

The results of the randomised clinical trial will be analysed according to the intention to treat principle. The effectiveness of labour induction at 41 weeks versus expectant management until 42 weeks will be assessed by calculating relative risks and 95% confidence intervals. Time to delivery will be compared using Kaplan-Meier curves and log-rank tests.

## Discussion

The policy regarding the timing of labour induction for (impending) post-term pregnancy is still under debate because of the inconclusiveness of the literature whether or not labour should be induced at 41 weeks or at 42 weeks for the prevention of adverse perinatal outcome. Most studies on labour induction or expectant management for (impending) post-term pregnancy started intervention beyond 41 weeks and continued expectant management far beyond 42 weeks. Until now, the Dutch guideline on post-term pregnancy indicates labour induction at 42 weeks. However, policy is moving towards labour induction at 41 weeks, though there is no consensus on this policy. This study will provide sufficiently precise and unbiased evidence on the difference between both strategies in perinatal and maternal outcome and patient preferences.

When our study shows that the incidence of poor neonatal and maternal outcome is very low and comparable with both strategies, this will in itself be an argument against intervention. Maternal preferences will then be leading in the choice between induction or expectant management. This study will help to achieve an evidence-based management strategy concerning impending post-term pregnancy.

We will adhere to the CONSORT guidelines for reporting the trial.
